## Abstract

**Background:**

Mass distributions of long-lasting insecticidal nets (LLINs) have contributed to large reductions in the malaria burden. However, this success is in jeopardy due in part to the increasing pyrethroid-resistant mosquito population as well as low LLINs coverage in various areas because the lifespan of LLINs is often shorter than the interval between replenishment campaigns. New insecticide-treated nets (ITNs) containing pyrethroid and piperonyl-butoxide (PBO) have shown a greater reduction in the incidence of malaria than pyrethroid LLINs in areas with pyrethroid-resistant mosquitoes. However, the durability (attrition, bio-efficacy, physical integrity and chemical retainment) of pyrethroid-PBO ITNs under operational settings has not been fully characterized. This study will measure the durability of pyrethroid-PBO ITNs to assess whether they meet the World Health Organization (WHO) three years of operational performance criteria required to be categorized as “long-lasting”.

**Methods:**

A prospective household randomized controlled trial will be conducted simultaneously in Tanzania, India and Côte d’Ivoire to estimate the field durability of three pyrethroid-PBO ITNs (Veeralin®, Tsara® Boost, and Olyset® Plus) compared to a pyrethroid LLIN: MAGNet®. Durability monitoring will be conducted up to 36 months post-distribution and median survival in months will be calculated. The proportion of ITNs: (1) lost (attrition), (2) physical integrity, (3) resistance to damage score, (4) meeting WHO bio-efficacy (≥ 95% knockdown after 1 h or ≥ 80% mortality after 24 h for WHO cone bioassay, or ≥ 90% blood-feeding inhibition or ≥ 80% mortality after 24 h for WHO Tunnel tests) criteria against laboratory-reared resistant and susceptible mosquitoes, and insecticidal persistence over time will be estimated. The non-inferiority of Veeralin® and Tsara® Boost to the first-in-class, Olyset® Plus will additionally be assessed for mortality, and the equivalence of 20 times washed ITNs compared to field aged ITNs will be assessed for mortality and blood-feeding inhibition endpoints in the Ifakara Ambient Chamber Test, Tanzania.

**Conclusion:**

This will be the first large-scale prospective household randomized controlled trial of pyrethroid-PBO ITNs in three different countries in East Africa, West Africa and South Asia, simultaneously. The study will generate information on the replenishment intervals for PBO nets.

## Background

Long-lasting insecticidal nets (LLINs) have contributed substantially to the reduction of the malaria burden over the past 15 years [1]. Between 2004 and 2020, more than two billion LLINs have been distributed worldwide [2]. Since the 1980s [3, 4], bed nets have been treated with pyrethroid insecticide because it has low toxicity to humans and non-targeted arthropods, and has a rapid insecticidal effect against susceptible malaria mosquitoes [5, 6]. Pyrethroid LLINs provide a physical barrier between humans and host-seeking mosquitoes, and the pyrethroid kill, incapacitate (knockdown), or inhibit feeding among mosquitoes that come into contact with the net [7, 8], enhancing bite protection even when the net is physically damaged [9]. When used with high coverage, LLINs provide community protection against malaria by reducing mosquito survival [7, 10–12].

Pyrethroid-resistant malaria vectors are now a major threat to the effectiveness of LLINs [13]. To tackle this threat, a new generation of insecticide-treated nets (ITNs) have been developed using pyrethroids combined with a synergist, such as piperonyl-butoxide (PBO) [12, 14]. PBO has little insecticidal activity by itself but acts as a synergist by blocking the oxidases (cytochrome P450) that commonly detoxify pyrethroid insecticides inside the mosquito’s body to restore pyrethroid efficacy [15–18]. Pyrethroid-PBO ITNs were found to yield a greater reduction in the incidence of malaria cases compared to standard pyrethroid LLINs for up to 21 months of use in areas with a high level of pyrethroid-resistance in mosquitoes [19] and have shown increased mosquito mortality compared to pyrethroid only LLINs in experimental hut studies when unwashed or after 20 washes [20]. However, in the Cochrane review of pyrethroid-PBO ITNs, the authors concluded that there is no evidence that PBO content persists under operational conditions for three years [20].

Bed nets that retain their bio-efficacy thresholds (the proportion of mosquitoes (≥ 95%) knocked down after one hour or (≥ 80%) mortality after 24 hours for cone bioassay, or if cone bio-efficacy thresholds are unmet, the proportion of mosquitoes (≥ 90%) blood-feeding inhibition or (≥ 80%) mortality after 24 h for tunnel tests) for at least 20 World Health Organization (WHO) standard washes under laboratory conditions and three years of recommended use under operational conditions are qualified as LLINs [8, 14]. However, it is not known if the 20 times WHO laboratory washed ITNs correspond to the field-used ITNs in inducing mosquito mortality. Also, although the WHO has prequalified several pyrethroid-PBO ITNs, there is currently limited data available on their physical and insecticidal durability under operational conditions in different geographical regions [8]. Understanding the durability of pyrethroid-PBO ITNs under operational conditions is important to guide procurement decisions and for devising replacement policies [21].

The physical integrity of a LLIN under operational conditions is one of the key determinants of net retention in the household, and more than 75% of discarded LLINs have damage and are perceived as failing to protect the user [22]. Factors associated with the loss of the physical integrity of LLINs include the environment in which the net is used [23–25], the users’ net care behaviour and attitude towards the LLIN [26], the type of net material [27–30], snag strength, bursting strength, abrasion resistance and resistance to hole enlargement [31], the number and age of people sleeping under the net [32, 33], and the geographical location in which the net is used [34]. Therefore, it is recommended to conduct ITN durability studies in multiple geographical locations [8]. The current study aims to measure the insecticidal and physical durability of three PBO ITNs alongside a pyrethroid only net over three years of household use in three different regions.

## Study objectives

### Overall aim

To evaluate the physical and insecticidal durability of PBO ITNs (Veeralin®, Tsara® Boost, Olyset® Plus) and a standard pyrethroid LLIN (MAGNet®) over 3 years of household use in Tanzania, East Africa, Côte d’Ivoire, West Africa and India, South Asia using standard WHO methods [8], and additionally to assess the non-inferiority [35, 36] of the PBO ITNs against Olyset® Plus.

### Secondary objectives

i.Estimate the attrition rate of each ITN product at 6, 12, 24 and 36 months of household use in each location.ii.Estimate fabric integrity of each ITN product at 6, 12, 24 and 36 months of household use in each location.iii.Estimate the bio-efficacy of each ITN product after 6, 12, 18, 24, 30 and 36 months of household use in each location.iv.Measure the insecticide content of each ITN product after 12, 24 and 36 months of household use in each location.v.Assess non-inferiority of field used Veeralin® and Tsara® Boost compared to Olyset® Plus and superiority of PBO ITNs compared to pyrethroid only MAGNet® from the Tanzania site after 12 and 24 months, upon the 24-h mortality primary endpoint.vi.Assess the equivalence of unwashed and 20 times laboratory washed nets and field-used ITNs after 12 and 24 months of each net type from the Tanzania site upon the 24-h mortality and blood-feeding inhibition endpoints.

## Methods

### Study area

This study will be conducted in selected villages in Tanzania, Côte d’Ivoire and India (Table 1). Study villages will be selected based on the availability of a large number of households required for the study, their accessibility throughout the year, the high abundance of malaria vectors that promotes mosquito net usage [37] and proximity to the bio-efficacy testing laboratory in each study country.

**Table 1 Tab1:** Description of study location in Tanzania, Côte d’Ivoire and India

Features	Tanzania	Côte d’Ivoire	India
Location of the study	Bagamoyo district in the Coastal region, located 70 km North of Dar Es Salaam	Tiassalé district in the Agnéby-Tiassa region, located 135 km North of Abidjan, in Southern Côte d’Ivoire	Kurnool district in the Andhra Pradesh state. Study villages are on the embankment of the river Tungabhadra
Global positioning system	Latitudes 6° 37ʹ South Longitudes 38° 58ʹ East	Latitude 5° 54′ North Longitude 4° 50′ West	Latitude 15° 81′ North Longitude 77° 96′ East
Tropical Climate	An average annual rainfall of 900 mm and temperature of 28 °C	An average annual rainfall of 1739 mm and temperature of 26.6 °C	An average annual rainfall of 705 mm and temperatures ranging from 26 to 46 °C in the summer and 12 °C to 31 °C in the winter
Economic activities of inhabitants	Most of the inhabitants are small-scale farmers	Most of the inhabitants are subsistence farmers and civil servants	Most of the inhabitants are small-scale subsistence farmers and civil servants

### Study design

This will be a prospective household-randomized controlled trial following WHO guidelines [8] for monitoring the durability of ITNs with slight modifications to the sample size and study procedures. A minimum of 6500 households from the selected villages in the study area will be enrolled in each country. In this study, a household is defined as a group of people who share living accommodation and who are eating from one pot. The households will be the unit of ITNs randomization and the individual nets as a unit of observation. At baseline, a household survey will be conducted to collect households’ information including demographic and socioeconomic characteristics and the location of the household. At the same time, mosquito nets will be distributed by a study team in each household to cover all sleeping places, to ensure maximum coverage of ITNs for all members of the household. Follow-up surveys will be conducted to assess the rate of net loss in the receiving households (attrition rates due to all causes, as well as for wear and tear), physical integrity, bio-efficacy and chemical residual content of ITNs collected from households at the time intervals up to 36 months (Table 2). The study flow diagram is shown below (Fig. 1). All participating households will be blinded to which net product they receive, and study investigators will also be blinded to intervention allocation.

**Table 2 Tab2:** Schedule of activities

Activities	Month							
	0	1	6	12	18	24	30	36
Conducted at baseline								
Community sensitization	x							
Household recruitment	x							
Baseline questionnaire	x							
Baseline bio-efficacy and chemical analysis	x							
ITNs distribution	x							
Conducted after baseline								
Adverse effects survey		x						
Monitoring the attrition			x	x		x		x
Monitoring fabric integrity for damage			x	x		x		x
Monitoring bio-efficacy using WHO bioassays			x	x	x	x	x	x
Chemical content analysis				x		x		x
Monitoring bio-efficacy using the IACT				x		x

**Fig. 1 Fig1:**
[figure not shown]
Study flow diagram showing the study procedures; attrition, fabric integrity assessment, bio-efficacy and chemical residual content will be done as per WHO guidelines [38]. The cross-sectional assessment of the non-inferiority and equivalences analysis will be conducted in Tanzania. *B* bioefficacy, *C* chemical analysis, *HH* household, *ITNs* insecticidal trated nets, *pHI* propotionate hole index, *TZ* Tanzania, *IACT* Ifakara Ambient Chember Test

The durability monitoring components that will be evaluated are: attrition, bioefficacy, chemical residual content, and damage to fabric. In addition, the Ifakara ambient chamber testing (IACT) will be conducted as an additional bioassay using nets sampled from the field in Tanzania, 20 times laboratory washed and unwashed nets.

### Study ITNs

Four different products of ITNs will be evaluated: Olyset® Plus, Veeralin®, Tsara® Boost and MAGNet® (Table 3). All test items have been prequalified by the WHO [39]. To ensure households and field workers are blinded to intervention allocation during the study, all ITNs will be rectangular in shape, white in colour, and of standard dimensions (190 cm × 180 cm × 150 cm) and will be labelled with a water-resistant six digits numeric self-laminating code attached to one of the six hanging loops. This code will uniquely identify each ITN and contain numbers representing the country, product, and individual net. Each product of ITN will be assessed at baseline in each country to ensure that they meet WHO bio-efficacy criteria before distribution (Table 4) using well-characterized laboratory-reared *Anopheles* mosquitoes [40] in the WHO cone bioassay or WHO tunnel tests if ITN do not meet the WHO cone bioassay criteria [8]. Insecticide content at baseline will be measured using appropriate Collaborative International Pesticides Analytical Council (CIPAC) methods, at an accredited laboratory.

**Table 3 Tab3:** Characteristics of durability study ITNs

Test item	Material type	Denier	Bursting strength (kPa)	Mesh size	Active ingredient	Estimated AI dose	Treatment method	Manufacturer	WHO status
Tsara® Boost	Polyethylene	130	≥ 400	21 holes/cm^2^	Deltamethrin and PBO	120 mg/m^2^ of deltamethrin and 440 mg/m^2^ of PBO	Incorporated	NRS Moon Netting FZE, United Arab Emirates	[67]
Olyset® Plus	Polyethylene	150	≥ 250	6.45 holes/cm^2^	Permethrin and PBO	800 mg/m^2^ of Permethrin and 400 mg/m^2^ of PBO	Incorporated	Sumitomo Chemical, Japan	[70]
Veeralin®	High-Density Polyethylene	130	≥ 350	13 holes/cm^2^	Alpha-cypermethrin and PBO	216 mg/m^2^ of alpha-cypermethrin and 79.2 mg/m^2^ of PBO	Incorporated	V.K.A Polymers, India	[68]
MAGNet®	High-Density Polyethylene	150	≥ 450	20 holes/cm^2^	Alpha-cypermethrin	261 mg/m^2^ of alpha-cypermethrin	Incorporated	V.K.A Polymers, India	[71]

**Table 4 Tab4:** ITNs durability components, outcome measured and analysis method

Component	Definition	Test conducted	Outcome indicators	WHO criteria or industry standard	Analysis method^c^
Attrition	Net loss from household through discarding or use for alternative purpose^a^	Households survey	Net presence	–	Logistic regression
Physical integrity	The physical state of the net to estimate bite protection	Count the number, location and size of the hole(s) of max. 3 nets per household	The holed surface area is measured by the proportionate Hole Index (pHI)^b^ [44] Median hole surface area (cm^2^)	pHI 0–64: good pHI 65–642: damaged pHI ≤ 642: serviceable pHI ≥ 643: too torn or unserviceable	Negative binomial regression, depending on distribution
Functional survival [44]	Estimation of nets still in households in serviceable condition	Presence or absence of net	(Number of nets present and serviceable)/(number of nets originally received and not given away or lost to follow up)	Median net survival in years = time point at which the estimate of functional survival crosses 50%	Logistic regression
Biological efficacy	The ability of the net to incapacitate or kill susceptible anopheline mosquitoes after contact with the insecticide	WHO cone/tunnel test using 25 × 25 cm pieces [8]	The proportion of net samples meeting the optimal WHO bio-efficacy criteria	1 h knock-down ≥ 95% or 24 h mortality ≥ 80% or blood feeding inhibition ≥ 90%	Logistic regression
		Ifakara Ambient Chamber Test (IACT) using whole nets	The proportion of mosquitoes dead at 24 h The proportion of mosquitoes not blood-fed	–	Logistic regression
Insecticide content	Amount of active ingredients in the net	Permethrin, Alpha-cypermethrin and piperonyl butoxide: Gas Chromatography with Flame Ionization Detection (GC-FID) Deltamethrin: High-Performance Liquid Chromatography with UV Diode Array Detection (HPLC–DAD)	The proportion of ITNs meeting with WHO specifications at baseline	MAGNet: 6 [4.5–7.5] g/kg alpha-cypermethrin Olyset Plus: 20 [15–25] g/kg permethrin; 10 [7.5–12.5] g/kg PBO Tsara Boost: 3 [2.25–3.75] g/kg deltamethrin; 11 [8.25–13.75] g/kg PBO Veeralin 6 [4.5–7.5] g/kg alpha-cypermethrin; 2.20 [1.65–2.75] g/kg PBO	Descriptive analysis

^a^Nets that are reported as given away, sold or stolen are not in the denominator (lost to follow up)

^b^Proportionate Hole Index (pHI): the number of holes of each size category measured in the field are weighted by the approximate surface area of the holes to provide a single measure of damage per net

^c^Analyses will include product, time point and village. Where more than one net per household is included in the analysis, a random effect for household will be included in the regression model

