### Monitoring bio-efficacy

#### Mosquito species

Pyrethroid susceptible and pyrethroid-resistant strains will be used for bio-efficacy testing in each country. Mosquitoes are maintained following MR4 guidance [48] by feeding larvae on Tetramin fish food and adults on blood meal between 3 and 6 days after emergence and 10% glucose solution ad libitum. All mosquitoes are maintained inside cages in different rooms to prevent cross-contamination. Temperature and humidity within insectaries are between 27 °C ± 5 °C and 70% ± 20% relative humidity, respectively.

In Tanzania, metabolic pyrethroid-resistant *Anopheles arabiensis* Kingani strain and a full pyrethroid susceptible *Anopheles gambiae *sensu stricto (s.s.) Ifakara strain will be used. In Côte d’Ivoire, metabolically resistant *An. gambiae* s.s. Tiassalé strain and a fully pyrethroid susceptible *An. gambiae s.s.* Kisumu strain will be used. In India, a pyrethroid-resistant *Anopheles culicifacies* strain and a fully pyrethroid susceptible *Anopheles stephensi* strain will be used. The bio-efficacy outcomes will be reported separately for each strain in each country. The susceptibility status of the susceptible and resistant strains will be confirmed at least twice per year in each country following standard procedures [49, 50] during the study period. If the susceptibility status changes during the study, a new colony will be established by either selecting resistant mosquitoes from a mixed colony or re-establishing a new colony from the original source.

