#### WHO cone test procedure

The WHO cone bioassays will be conducted separately at the (1) Vector Control Product Testing Unit (VCPTU) in Bagamoyo, Tanzania, (2) Swiss Centre for Scientific Research (CSRS) in Tiassalé district, Côte d’Ivoire, and 3) ICMR-National Institute of Malaria Research (NIMR) field unit in Bengaluru, Karnataka state, India. Four cones will be attached to each net piece and 5 mosquitoes exposed per cone, 100 mosquitoes per strain at baseline and 80 mosquitoes per strain at each post-distribution survey to each ITN [8]. Non-blood-fed, 2–5 days old, female mosquitoes each of the susceptible and resistant strains for the PBO nets and susceptible strain for the pyrethroid only net will be exposed to the ITN for 3 min [8]. After the exposure, mosquitoes will be removed and kept in holding cups provided with 10% glucose or sucrose solution. Mosquito knockdown will be recorded after 60 min (KD_60_) and mortality after 24-h (M_24_). ITNs that do not meet WHO bio-efficacy thresholds of KD_60_ ≥ 95% or M_24_ ≥ 80% with the susceptible mosquito strains will be tested in the WHO tunnel test [8].

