#### The sample size for the entomological outcomes in the IACT

Simulation was used to determine the sample size for the bio-efficacy testing of ITNs in the IACT. Each PBO net product will be assessed for non-inferiority against Olyset® Plus on mortality at 24 h. Each product will have sixty nets some tested more than one times for 72 nights with 15 mosquitoes per strain per chamber per night. From a previous study (author, pers.commun.), the variation between individual field-aged nets per product was assumed at a standard deviation of 0.1 and between chamber-nights at 0.15, both on the log-odds scale. Assuming mortality of 70% for the PBO nets and Olyset Plus, 1000 simulation trials were conducted to assess non-inferiority for each trial and the power estimated by the proportion of trials that showed non-inferiority where the product was indeed non-inferior, was over 80%.

To assess the equivalence of field nets to 20-times washed nets on mortality, each product consisting of sixty replicates of field-aged nets as well as four replicates of twenty times laboratory washed and unwashed nets will be tested 54 times (three rounds with 18 replicates each). Assuming 70% mortality for each product of field and washed nets, and assuming 0.1 standard deviation between individual replicate nets per product and a chamber-night standard deviation of 0.15 on the log-odds scale, using 15 mosquitoes per strain per chamber per night, the study is powered at 80%.

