## Discussion

This study is the first large-scale prospective household randomized controlled trial of PBO ITNs in three different countries simultaneously. It will allow a pooled estimate of ITN durability from three countries, enabling precise estimates of product performance over time.

In a cluster randomized trial that assessed the effectiveness of Olyset® plus, there was a high washout of PBO concentration within 21 months of use under operational conditions [19] and more than 97% washout after 3 years [63]. Similarly, Olyset® Plus lost more than 87% of PBO concentration after 3 years in Kenya [64]. In Uganda, more than 55% of PBO concentration in Olyset® Plus was washed out within 25 month [65]. These publications highlight the importance of describing the estimated period of performance of PBO ITNs in different contexts. This study will report the persistence of PBO and pyrethroid concentrations in Olyset® Plus, Veeralin®, and Tsara Boost® beside pyrethroid concentration in MAGNet® for the period of 3 years of use in the field in three locations. It will also monitor the added value of PBO against resistant strains of mosquitoes over time as recommended for durability monitoring of products designed to kill pyrethroid-resistant malaria vectors [66].

PBO ITNs including Veeralin® and Tsara® Boost are currently recommended as pyrethroid only ITNs [67, 68] and are required to demonstrate non-inferiority using 24-h mortality and feeding inhibition endpoints compared to the first-in-class Olyset® Plus [69]. This study will measure the non-inferiority of Veeralin® and Tsara® Boost compared to the Olyset® Plus, collected from the field operational settings i.e. the non-inferiority as part of product durability evaluation. Currently, twenty times washed, deliberately holed ITN is used as a reasonable proxy for a field aged net. This study will explore whether this assumption is acceptable, or if it should be revised.

The results of this trial will provide robust and rigorous evidence of the likely replenishment interval, quality and additional bio-efficacy of PBO ITNs compared to pyrethroid only ITNs up to 3 years after the distribution.

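### Cone and tunnel bio-efficacy against the resistant strain is planned only as a per-net pass/fail, which cannot rank products or show decline when mortality lies below the 80% cut; the recorded counts should be analysed beside it

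*Protocol article*

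**What the plan says.** The Biological efficacy row of Table 4 (Protocol article, Study ITNs) gives the cone/tunnel outcome as "The proportion of net samples meeting the optimal WHO bio-efficacy criteria". A net passes on any one of three limbs: 1-h knockdown of at least 95%, 24-h mortality of at least 80%, or blood-feeding inhibition of at least 90%. The analysis is logistic regression and, by footnote c, includes product, time point and village. Data analysis refers the durability outcomes back to this table.

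The same row defines the component as "The ability of the net to incapacitate or kill susceptible anopheline mosquitoes after contact with the insecticide". The WHO cone test section likewise uses the susceptible strain to trigger the tunnel test: nets that miss the thresholds "with the susceptible mosquito strains will be tested in the WHO tunnel test". The abstract, however, speaks of "criteria against laboratory-reared resistant and susceptible mosquitoes, and insecticidal persistence over time will be estimated", and the Mosquito species section says: "The bio-efficacy outcomes will be reported separately for each strain in each country".

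PBO nets are cone-tested with both strains, at 80 mosquitoes per strain per net at each follow-up survey, and 60-minute knockdown (KD60) and 24-h mortality (M24) are recorded. Thirty nets per product are tested at 6 to 30 months and 50 at 36 months. Mosquito-level mortality appears as an outcome only for the IACT, which uses nets from Tanzania at 12 and 24 months.

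**The concern.** There are two linked problems.

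First, the article is not consistent about whether the pass/fail criteria apply to the resistant strain. Table 4 and the tunnel trigger point to the susceptible strain; the abstract and the reporting by strain point to both. Because the trigger is the susceptible result, a PBO net that misses the cut only against the resistant strain never reaches the tunnel. It is therefore unclear what meeting the combined criterion means for that strain.

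Second, if pass/fail is the resistant-strain outcome, each net's 80 mosquitoes are reduced to one yes/no. In Côte d'Ivoire and India at every survey, and in all three countries at 6, 18, 30 and 36 months, that is the only planned resistant-strain result. Two products at 60% and 40% mortality, or one product falling from 60% to 40%, could both score close to 0 of 30 passing nets. With an empty cell the logistic model has no finite odds ratio. The Discussion sets the aim of following performance over time: "It will also monitor the added value of PBO against resistant strains of mosquitoes over time as recommended for durability monitoring". A single cut at 80% cannot show what happens below it.

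**Working it through.** **What the protocol gives.** It states no power, expected mortality or variance for the cone or tunnel test. The nearest figures come from the IACT sample-size section: "Assuming mortality of 70% for the PBO nets and Olyset Plus", a between-net SD of 0.1 and a chamber-night SD of 0.15, both on the log-odds scale, and power over 80%. That statement reproduces. With 126 replicates of 15 mosquitoes and 60 nets per arm,

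variance per arm = 1/(126×15×0.7×0.3) + 0.15²/126 + 0.1²/60 = 0.00252 + 0.00018 + 0.00017 = 0.00287;

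SE of the difference = √(2×0.00287) = 0.0757;

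power against an odds ratio of 0.7 = Φ(0.3567/0.0757 − 1.96) = 99.7%.

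These inputs are therefore coherent for the IACT. Using them for the cone test is an assumption of this review.

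**Pass probability, mortality limb only.** A net passes with at least 64 of 80 dead (80%).

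- At 70% true mortality and no net variation: P(X ≥ 64), X ~ Bin(80, 0.7), = 3.0%.
- With net SD √(0.1² + 0.15²) = 0.18: 6%.
- With an assumed net SD of 0.5: 19%; with 1.0: 31%.

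**Power, pass/fail v mortality.** Two groups of 30 nets, 80 mosquitoes per net, net log-odds drawn from a normal distribution, two-sided 5%. Pass/fail is compared by a likelihood-ratio logistic test, mortality by a t-test on deaths per net. Each row rests on at least 4,000 simulated comparisons (Monte Carlo SE at most √(0.25/4000) = 0.8 points). The two groups can be two products, or one product at two surveys, since sampled nets are withdrawn and their households are not sampled again.

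| Net SD | True mortality | Expected pass rates | Pass/fail power | Mortality power |
|---|---|---|---|---|
| 0.18 | 80 v 70% | 55%, 6% | over 99% | 100% |
| 0.18 | 75 v 70% | 23%, 6% | 50% | 87% |
| 0.18 | 70 v 65% | 6%, 1% | 20% | 82% |
| 0.18 | 70 v 60% | 6%, 0.1% | 27% | 100% |
| 0.18 | 60 v 50% | 0.2%, 0% | 0% | 100% |
| 0.5 | 80 v 70% | 53%, 19% | 81% | 95% |
| 0.5 | 70 v 60% | 19%, 5% | 46% | 86% |
| 0.5 | 60 v 40% | 5%, 0.1% | 18% | 100% |
| 1.0 | 80 v 70% | 52%, 31% | 36% | 50% |
| 1.0 | 70 v 60% | 31%, 18% | 25% | 37% |
| 1.0 | 60 v 40% | 18%, 5% | 45% | 84% |

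At 36 months (50 nets, SD 0.18), 70 v 65% gives 36% v 96%. For 70 v 60% at SD 0.18 with 30 nets, at least one group has no passing net in 96% of simulated comparisons. The likelihood-ratio test favours pass/fail: a pooled z-test gives about 10% for the same case.

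**The knockdown limb.** A net also passes with at least 76 of 80 knocked down. Without net variation the chance is 9% at a true KD60 of 90%, 63% at 95% and 91% at 97%. The protocol gives no expected knockdown or feeding inhibition, so the overall pass rate cannot be derived from it.

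**The case against.** The strongest reply is that the outcome fits the stated question. The abstract asks whether nets meet the WHO operational criteria, which is a pass/fail matter. The cone/tunnel objective is to estimate bio-efficacy, and no powered product comparison is promised for it. Formal comparison is assigned to the IACT, where mortality is analysed per mosquito. This stands as a reason to keep the pass rate. It does not remove the point, because footnote c already plans regression on product and time point, and because the IACT covers one country and two time points.

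A reader might infer that, at the protocol's own assumed mortality, the resistant-strain pass rate will sit near 0%. The documents do not support that. The 70% and the SDs are IACT assumptions for whole nets exposed overnight, with no strain named; the cone test exposes mosquitoes to cut pieces for 3 minutes. The criterion is either/or, so knockdown or feeding inhibition could carry the pass rate well above zero. Even on mortality alone it is 19% to 31% at the larger SDs.

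A reader might also infer that most power is lost generally. That is not so: 80 v 70% keeps over 99% power at SD 0.18.

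Nor can a cone analysis of the resistant strain measure PBO against pyrethroid-only nets, because MAGNet is cone-tested with the susceptible strain only. It can compare PBO products and follow each over time.

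Finally, one could say that Table 4 covers susceptible mosquitoes only and leaves the resistant-strain model to a fuller plan. On that reading the abstract's use of the criteria for both strains still needs reconciling.

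**Conclusion.** The point holds in a limited form. The article fixes a per-net pass/fail as the only cone/tunnel outcome, is inconsistent about whether it applies to the resistant strain, and plans no analysis of resistant-strain mortality outside the IACT. For differences lying below the 80% cut, pass/fail is clearly the weaker analysis at every SD tried. For 70 v 60% with 30 nets the gap is about 73 points at SD 0.18, 40 at SD 0.5 and 12 at SD 1.0.

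These sizes are illustrative. They rest on borrowed or assumed mortality and variance, and on nets not passing by knockdown or feeding inhibition. If nearly all nets pass on knockdown, the pass rate sits near its ceiling and is again uninformative about mortality. The documents do not say which case will arise, which is itself a reason not to rely on the pass rate alone. The attrition outcome that drives the survey sample size is untouched.

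**What to change.** In Table 4:

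1. Keep the WHO pass rate as an outcome for both strains, since the abstract names it.
2. Reconcile the definition of biological efficacy with the abstract, and state whether the thresholds apply to the resistant strain and how the cone and tunnel results combine for it.
3. For the resistant strain (PBO nets), add 24-h mortality and KD60 in the cone test, and mortality and blood-feeding inhibition in the tunnel test. Analyse them as counts per net in a logistic model with product, time point, their interaction and village (village as in footnote c) and a random effect for net, by country.
4. Note that tunnel results come only from nets that missed the cone criteria with the susceptible strain, so they describe that subset.

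The cost is a few added reported outcomes, a short edit to Table 4 and a few lines of code. The cone counts are already recorded, and the tunnel section already provides for mortality and feeding to be recorded, so no further testing is needed. The article reports that follow-up is in progress, so the change should be dated and made before resistant-strain results are compared by product.
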